## Abstract

**Background:**

Human umbilical cord blood (HUCB) serum eye drops contain growth factors, neurotrophic agents, and antimicrobial compounds that may promote ocular surface healing and regeneration. Sjögren’s syndrome is a chronic autoimmune condition characterized by reduced tear production and ocular surface damage, often resulting in severe dry eye symptoms. Mustard gas chemical veterans also suffer from similar debilitating ocular complications due to chronic inflammation and meibomian gland dysfunction. While conventional treatments offer symptomatic relief, they lack essential components of natural tears.

**Materials and methods:**

This pilot randomized controlled trial will evaluate the efficacy of HUCB eye drops in three patient groups: (A) Sjögren’s patients treated with HUCB drops, (B) Sjögren’s patients receiving conventional treatment, and (C) mustard gas veterans receiving conventional treatment in the right eye and HUCB drops in the left eye. Patients will be assessed using subjective and objective tools, including the Ocular Surface Disease Index (OSDI), visual acuity, tear film breakup time (TBUT), SM tube test, and fluorescein staining based on SICCA criteria. Group allocation will follow a blocked randomization sequence for groups A and B; group C will follow a within-subject paired-eye design. Follow-up will occur at 30 and 60 days.

**Discussion:**

This study aims to assess the regenerative potential of HUCB serum in patients with autoimmune and chemically induced dry eye. Its results may support broader clinical use of HUCB drops in treating severe ocular surface disorders, including conditions like Stevens-Johnson syndrome and industrial chemical exposures.

**Trial registration:**

This trial was registered at the Iranian Registry of Clinical Trials (Registration number: **IRCT20230925059512N1**, Registration date: **2024-08-11**).

## Background

Sjögren’s syndrome is a chronic autoimmune disease that primarily affects exocrine glands, particularly the salivary and lacrimal glands. This leads to dry mouth and eyes as a common symptom in patients. However, it is often associated with musculoskeletal disorders and Inflammatory processes damage to other body systems [1]. The diagnosis of Sjogren’s syndrome is based on a combination of dryness symptoms and autoimmune features, including T-cell activity (confirmed by a positive salivary gland biopsy) or B-cell activity (demonstrated by the presence of autoantibodies) [2]. In most cases, Sjogren’s syndrome occurs independently of other inflammatory and autoimmune diseases and is referred to as primary Sjogren’s syndrome. However, it can also occur together with other autoimmune diseases such as thyroid disease, rheumatoid vasculitis and systemic lupus erythematosus, which is referred to as secondary Sjogren’s syndrome [3]. An increased prevalence of dry eye is observed in patients with autoimmune diseases, including Sjogren’s syndrome. Approximately 8% of the population is affected by this disease, 78% of whom are women [4,5]. Dry eye is typically due to instability of the tear film, with the thickness of the lipid layer being a key factor in this stability [6]. Chronic inflammation combined with decreased secretion of tear fluid and increased evaporation contribute to its development [7]. Patients with dry eye may complain of foreign body sensation, pain, sensitivity to light, blurred vision and difficulty opening the eyes. [8] Tears contain various growth factors and essential compounds, including epidermal growth factors, vitamin A, neurotrophic factors, albumin, and specific and non-specific antimicrobial substances such as lysozyme, lactoferrin, alpha-lysine and protein-based antimicrobial components. These elements play an important role in maintaining the health of the epithelial surface of the eye [9,10]. Lysozyme destroys bacteria by hydrolyzing the peptidoglycan layer of bacterial cell walls. In addition, lysozyme also has antifungal properties due to its ability to degrade chitin [10,11]. Alpha-lysine disrupts cell membranes by an unclear mechanism, and its concentration in tears is higher than in serum or plasma [12]. Lactoferrin reversibly binds to two iron atoms, limiting bacterial access to iron, which is critical for their growth and metabolism [13]. Specific antimicrobial components in tears include immunoglobulins A, G and M [14].

The tear film provides a smooth optical surface for the refraction of light, nourishes the cornea and plays a crucial role in the eye’s defense system. A lack of tear production or a change in tear composition can lead to eye damage and pathological conditions [15].

Long-term ocular complications resulting from exposure to chemical warfare agents include photophobia (73.2%), perceived visual deterioration (72.5%), dry eye sensation (66.4%), foreign body sensation (61.1%), excessive tearing (46.3%) and pain (43%). Slit lamp findings indicate meibomian gland dysfunction (96%), eyelid inflammation, tear abnormalities and dry ocular surfaces (80–90%). Chronic eyelid inflammation and decreased tear secretion are two key factors contributing to the progression of these ocular complications. The likelihood of chemical-induced keratopathy increases with higher initial exposure, higher degree of disability and longer duration of ocular involvement [16].

Initial ocular symptoms of chemical agent exposure include lacrimation, edema, ocular discharge, and even blindness, which may gradually resolve over the course of days or weeks. However, residual keratopathy may remain, leading to long-term effects in affected individuals (DMGK). Patients often suffer from dry eye symptoms [17].

Current treatments for dry eye syndrome include artificial tears, topical corticosteroids, cyclosporine A, therapeutic contact lenses, protective eyewear, punctal occlusion and tarsorrhaphy. However, these methods do not provide the essential growth factors and components found in natural tears [18].

Eye drops derived from the umbilical cord blood of healthy mothers contain high levels of cytokines, vitamin A, growth factors, neurotrophic factors and essential tear components, as well as antibacterial and antifungal agents such as IgG, lysozyme and other compounds. These drops create a suitable environment for the growth and regeneration of damaged cells and tissues. They are preservative-free, safe and effective in promoting the repair and regeneration of damaged epithelial cells and improving epithelial diseases [9,19,20].

Human umbilical cord blood serum (HUCB) eye drops are a safe and effective treatment rich in growth factors, essential tear components, neurotrophic and defensive factors. These drops not only provide the necessary tear components, but also provide an ideal environment for the regeneration and repair of damaged tissue. With a structural composition very similar to natural tears, they have shown significant efficacy in the treatment of dry eyes and ocular surface disorders.

However, its specific therapeutic effects in patients with Sjogren’s syndrome — a condition characterized by combined lacrimal gland dysfunction and ocular surface damage — and in chemical warfare veterans suffering from severe dry eye and extensive ocular surface damage, including corneal and conjunctival lesions, have not yet been thoroughly investigated. Although the underlying causes differ (autoimmune vs. chemical injury), both conditions share common pathogenic mechanisms — including epithelial damage, tear film instability, and chronic inflammation. Therefore, investigating HUCB serum in these two distinct but mechanistically related populations provides an opportunity to evaluate its regenerative potential across different etiologies of severe dry eye.

This study aims to investigate the effects of HUCB eye drops:

The improvement and repair of damaged ocular surface tissue.The restoration of vision diminished by damage to the ocular surface tissue.The relief of severe dry eye symptoms in patients with Sjogren’s syndrome and chemical warfare veterans.

Both subjective and objective tests will be used to evaluate these outcomes. The results of this study may also have application to other eye conditions associated with severe dry eye and ocular surface damage, such as Stevens-Johnson syndrome, keratoconjunctivitis sicca, burns, and chemical warfare or industrial exposure injuries.

## Materials and methods

### Study design and setting

This randomized, controlled, and open-label clinical trial will be conducted in the Baqiyatallah University of Medical Sciences, Tehran, Iran. Patients will enter the study based on the eligibility criteria and will be followed until 60 days post-intervention. We began participant recruitment on April 1, 2025, and estimate that the participant recruitment will be completed by July 31, 2025, data collection will end by September 30, 2025, and the results are expected to be ready by October 31, 2025.

This pilot trial includes two distinct yet related populations: (1) patients with Sjögren’s syndrome, and (2) mustard gas–exposed veterans with chronic dry eye. The analyses will be conducted independently for these groups, as they represent separate exploratory sub-studies designed to assess feasibility and estimate effect sizes in autoimmune and chemically induced dry eye, respectively.

### Ethical approval

This protocol was approved by the Research Ethics Committee of the Baqiyatallah University of Medical Sciences and is in accordance with the ethical principles and the national norms and standards for conducting medical research in Iran (Approval ID: IR.BMSU.BAQ.REC.1403.080, Approval Date: 2024-06-29). Also, this trial was registered at the Iranian Registry of Clinical Trials (Registration number: **IRCT20230925059512N1**, Registration date: **2024-08-11**).

### Outcome measures

#### Primary outcome (dry eye symptoms).

To assess subjective symptoms of dry eye, the Persian version of the OSDI questionnaire, which has been validated and shown to have good reliability and validity in the Iranian population, will be used [21].

### Procedure

In brief, all the assessments and evaluations are presented in **Table 1**.

**Table 1 pone.0337186.t001:** Project assessment and time steps.

Procedures	Screening Day −1	Intervention Day −1	Study Visit 1 Day 30	Study Visit 2 Day 60
Written informed consent	X			
Demographics	X			
Medical history	X			
Randomization	X			
Administer study intervention		X		
Concomitant medication review	X	X	X	X
Performance status	X			
REFRACTION (OU)	X		X	X
BCVA (Log MAR)	X		X	X
OSDI questionnaire	X		X	X
TBUT (s)	X		X	X
Tear meniscus height (TMH)	X		X	X
SM tube test	X		X	X
Corneal staining (SICCA):	X		X	X
Conjunctiva staining TEMPO (SICCA)	X		X	X
Conjunctiva staining NASAL (SICCA)	X		X	X
Adverse event review and evaluation	X	X	X	X
Complete Case Report Forms (CRFs)	X	X	X	X

#### Recruitment and baseline assessment.

Individuals who visit Baqiyatallah Hospital and meet the criteria for participation in the study will be assessed by a rheumatologist. Those with a confirmed diagnosis of Sjögren’s syndrome, based on rheumatological factors and clinical findings, including a combination of dry eye symptoms and autoimmune characteristics (such as T-cell activity, confirmed by a positive salivary gland biopsy, or B-cell activity, confirmed by the presence of autoantibodies), will be referred to the ophthalmology clinic. If they agree to participate, they will be included in the study.

Additionally, individuals with moderate to severe mustard gas chemical eye injuries who exhibit dry eye symptoms, as diagnosed by an experienced ophthalmologist, will also be included in the study.

For the control group, standard treatments for dry eye, such as artificial tears and topical corticosteroid drops, will be used, and the changes will be monitored. A convenience sampling method will be used, and the study’s purpose will be clearly explained to participants. Written informed consent will be obtained from all participants.

#### Umbilical cord serum droplets.

After childbirth, umbilical cord blood was collected directly as part of this study by the research team at Baqiyatallah University of Medical Sciences, Tehran, Iran. The collection took place in affiliated hospitals under ethical approval and informed written consent from the donor mothers. All cord blood samples were obtained in sterile containers without anticoagulants and were immediately processed under controlled laboratory conditions.

We included women aged 18–45 without any current known infection who underwent elective cesarean section. Also, in laboratory conditions, the donated umbilical cord blood samples are screened for contagious viral pathogens such as Human Immunodeficiency Virus (HIV), syphilis, and hepatitis B and C viruses. These samples will be taken in the same timeline as the rest of the study. We began recruitment of eligible donor mothers on April 1, 2025, and estimate that it will be completed by July 31, 2025.

The virus-free umbilical cord blood is incubated for two to four hours at room temperature, followed by the blood centrifugation process. After centrifugation, the yellow supernatant (serum) is carefully separated into a new sterile tube, and the remaining sediment (red blood cells and other cellular debris) should be discarded. Thermal inactivation should then be carried out at 56°C for 30 minutes on the collected serum. Following inactivation, filtration is performed, and the serum is stored at −20°C for future clinical use.

Serum eye drops, including autologous serum eye drops (ASEDs) and umbilical cord blood serum (UCBS), are advanced biologic treatments used to manage severe ocular surface diseases.

Opened serum drops should be stored in the refrigerator at 4°C within 7 days to ensure safety and effectiveness due to the lack of preservatives and risk of contamination, while unopened drops should be kept at −20°C for up to 3 months. The serum drops are administered 6–10 times a day, and if necessary, preservative-free artificial tears may also be recommended [25].

### Eligibility criteria

Patients with Sjögren’s syndrome and victims of chemical eye injuries who suffer from severe dry eye symptoms and do not respond well to conventional dry eye treatments will be included in the study. These individuals will have a short tear break-up time (less than 5 seconds), low SM tube results (less than 5 mm), and positive fluorescein staining of the cornea and conjunctiva (≥3).

### Intervention

The participants are divided into three groups:

**Intervention group A:** Patients with definite diagnosis of Sjogren’s and dry eyes.

**Control group B:** For the control group, conventional dry eye treatment methods (standard of care).

**Intervention group C:** Mustard gas chemical veterans with dry eye symptoms.

In the group A patients, after performing the desired tests, we will give the patient eye drops made from umbilical cord blood serum and will ask them to put one drop in each eye 6–10 times a day. For the group B, conventional dry eye treatment methods such as artificial tear drops and topical corticosteroid drops will be used and the changes will be monitored. In the group C, patient’s right eye will be treated with conventional methods such as artificial tears and Flucort drops, and one drop of cord blood serum will be dropped in the left eye, 6–10 times a day.

### Randomization

A randomized list with block size of 2 will be generated using the Sealed Envelope website [26]. The sequence of participants in the list will be available only to an external observer responsible for participant allocation, that will not participate in the other parts of the study. The randomization will be performed only for groups A and B. Patients in group C will get conventional treatment in their right eyes and umbilical cord serum in their left eye.

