### Blinding and study termination

This study will be an open label study that only the assessing optometrist and ophthalmologist will not be aware of the participant allocation and the participants, external observer responsible for participant allocation, and the physician performing the intervention will be aware of the patient allocation.

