### Concealment

We will be using sealed envelopes for concealment.

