### Sample size

Given the pilot nature of the study, no formal sample size calculation was conducted. However, the results will be used to estimate effect sizes and variability to inform future definitive trials. we will include 10 patients in each group of the study. This number was also determined based on available resources, expected recruitment rates, and the exploratory aim of generating effect size estimates for planning a future definitive trial. Since the number of mustard gas veterans are limited, we will be using each patient of this group as their own controls.

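### A single fixed block size of 2 in an open-label, single-centre trial lets the second allocation of every A/B pair be deduced, despite the sealed envelopes

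*Protocol article*

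**What the plan says.** The Randomization section of the Protocol article gives one block size and no others: "A randomized list with block size of 2 will be generated using the Sealed Envelope website". It limits the list to the Sjögren's patients ("The randomization will be performed only for groups A and B"), and the Sample size section sets the number: "we will include 10 patients in each group of the study". That makes 20 randomised patients in 10 blocks.

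Two safeguards are stated. Under Randomization, "The sequence of participants in the list will be available only to an external observer responsible for participant allocation", and that person takes no other part in the study. Under Concealment, "We will be using sealed envelopes for concealment".

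The trial is open label. Under Blinding and study termination, participants know their arm and "the physician performing the intervention will be aware of the patient allocation"; masking is confined to the outcome assessors ("only the assessing optometrist and ophthalmologist will not be aware of the participant allocation"). The study runs at one university, and under Recruitment and baseline assessment, "A convenience sampling method will be used". Table 1 places consent, randomization and the baseline OSDI in the same screening column without giving their order.

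**The concern.** Envelopes and a restricted list stop staff from seeing the next assignment. They cannot stop staff from working it out. With blocks of two the only possible blocks are AB and BA, so once the first patient of a pair is openly treated, the second patient's arm is settled.

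Whoever decides whom to enter, and when, could then choose a patient for a known slot. There is room for choice: sampling is by convenience, and eligibility rests partly on judgement (severe symptoms, poor response to conventional treatment) alongside measured thresholds.

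A versus B is the only randomised comparison. Its OSDI effect size and standard deviation are meant to inform the sample size of a definitive trial, so a selection bias here would be carried into that trial's planning.

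There is also a lesser concern about masking. An assessor who learns one patient's arm and the entry order also learns the arm of the other patient in the pair.

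**Working it through.** The article gives no figure for predictability, so there is none to reproduce.

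**Inputs from the article:** block size 2, fixed (Randomization); 10 patients in each of A and B, so N = 20 and 20/2 = 10 blocks (Sample size); past allocations known to participants and the treating physician (Blinding and study termination).

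**Assumption:** the person guessing knows the block size, the entry order and the earlier arms, and always guesses the arm with more places left in the block.

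**Blocks of 2**
- Certain allocations: one per block, 10 × 1 = 10 of 20 (50%).
- Expected correct guesses: (10 × 0.5 + 10 × 1)/20 = 15/20 = 75%.

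**One permuted list of 10 A and 10 B (n = 10 per arm)**
- Certain allocations, the run left once one arm is full: 2n/(n + 1) = 20/11 = 1.8 of 20 (9%).
- Expected correct guesses: [n + (2^(2n)/C(2n, n) − 1)/2]/(2n) = [10 + (1,048,576/184,756 − 1)/2]/20 = 12.34/20 = 61.7%.
- Exact enumeration gives the same values.

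**Comparison for N = 20**

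| Scheme | Certain in advance | Correct guesses |
|---|---|---|
| Fixed blocks of 2 (plan) | 10 (50%) | 15.0 (75%) |
| Fixed blocks of 4 | 6.7 (33%) | 14.2 (71%) |
| Undisclosed mix of 4 and 6 | not computed | 13.7 (about 69%) |
| One list of 20 | 1.8 (9%) | 12.3 (62%) |
| Simple randomisation | 0 | 10.0 (50%) |

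The row for the mix comes from 100,000 simulated lists, guessing the arm that is behind in the running totals.

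**What steering could do to the estimate.** The article gives no figure for steering, so delta is an assumed shift in the outcome of a steered patient: +delta in a known A slot, −delta in a known B slot. Let k of the 10 known slots be A, so 10 − k are B; on average k = 5.
- No steering: bias 0.
- All known slots, both directions: (k/10)·delta + ((10 − k)/10)·delta = delta, whatever k is.
- All known slots of one arm only: on average (5/10)·delta = 0.5 delta.
- Half of the known slots, both directions: on average (2.5/10)·delta + (2.5/10)·delta = 0.5 delta.

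For an assumed delta of 0.3 SD, the range is 0 through 0.15 SD to 0.3 SD.

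**The case against.** The strongest reply is that predictability is not bias. To use it, a person must know the block size, the entry order and the preceding arm, and must also influence who enters. The article gives the arms to the treating physician but does not say that this physician enrols patients. A rheumatologist assesses and refers patients, and an external observer allocates. This stands: steering is a plausible route, not a documented one. On the other hand, only the external observer is barred from other roles, and nothing states that the block size is withheld from recruiting or treating staff.

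A reader might infer that concealment fails altogether. It does not, because the first slot of each pair stays concealed. A reader might also infer that printing the block size in the article tipped off recruiters. No publication date is shown against the planned recruitment of April to July 2025, so that cannot be assumed; the argument needs only staff who know the protocol.

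There is some mitigation. Eligibility has measured thresholds (TBUT below 5 s, SM tube below 5 mm, staining 3 or more). OSDI is taken at screening, and the regression is described as giving an adjusted difference. If baseline OSDI is among the covariates, part of any selection on severity is removed; selection on unmeasured prognosis is not.

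Finally, this is a pilot that disclaims definitive inference. With 10 per arm the unadjusted 95% confidence interval has a half-width of about 2.10 × √(2/10) = 0.94 SD, so a 0.3 SD bias would be about a third of that. This lowers the weight of the point but does not remove it: estimation is the stated goal, and the interval does not allow for selection bias.

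**Conclusion.** The concern holds as a point about predictability. Under the stated scheme 10 of 20 A/B allocations can be deduced and 75% guessed on average, against about 1.8 of 20 and 62% for a single list of the same size and final balance. This follows from the stated block size and open treatment, given the knowledge assumed above, and the two stated safeguards do not reach it.

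Realised bias is a different matter. The document does not show that anyone who enrols patients knows the preceding arm, so the bias is a risk between 0 and delta. A reader might take a single value such as 0.3 SD as the expected bias. That value is an assumption, and reaching it requires steering every known slot in both directions.

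Assessor unmasking is conditional and secondary. It needs a leak of one arm plus the entry order, which the article does not say assessors have. It would mainly affect the secondary outcomes, since the primary OSDI is reported by participants who already know their treatment. Group C is not on the list and is unaffected.

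The change is worth making because it is cheap and protects the only randomised comparison.

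**What to change.** Replace the blocks of 2 with one computer-generated permuted list, held by the external allocator, containing the places still open in each arm. That is 10 A and 10 B if nobody has been allocated; otherwise it is the remaining number per arm, since a fresh 10 and 10 list would lose the final balance. Undisclosed, randomly varying larger blocks are a weaker alternative (about 69% guessable for a mix of 4 and 6). Open each envelope only after eligibility and baseline OSDI have been recorded.

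The cost is regenerating the list, with no extra patients or staff. The downsides are a mid-trial change that must be documented if recruitment is under way, and possible temporary imbalance between the arms if recruitment stops early.

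If allocation is already complete, report the predictability of every second allocation as a limitation of the A/B comparison.

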### Statistical analysis

All statistical analyses will be performed using Stata version 17.0. The analysis will focus on estimation rather than formal hypothesis testing, in line with the pilot nature of this trial. The primary goal is to generate effect size estimates and their corresponding 95% confidence intervals to inform the design of a future definitive trial. A p-value of < 0.05 will not be interpreted as definitive evidence of a treatment effect due to the small sample size.

Descriptive statistics will be used to summarize baseline characteristics of participants across the three groups. Continuous variables will be reported as mean ± standard deviation (SD), and categorical variables will be expressed as frequencies and percentages.

To estimate the effect of the intervention in group A vs. B comparison, regression-based modeling will be employed. For continuous outcomes, a linear regression model will be used. The β coefficient will represent the adjusted mean difference in the outcome between the HUCB and conventional treatment groups. Its 95% confidence interval will provide a range of plausible effect sizes. For binary outcomes, a logistic regression model will be used. The exponentiated coefficient for the treatment group will be reported as an Odds Ratio (OR) with its 95% confidence interval.

For Group C, which uses a paired-eye design, a linear mixed-effects model will be used to account for the non-independence of two eyes from the same patient. The model will include treatment (HUCB vs. conventional) as a fixed effect and a random intercept for each patient. The primary output will be the estimated mean difference between treatments and its 95% confidence interval.

The effect size and standard deviation of the OSDI score (primary outcome) will be used to inform future sample size and power calculations for a definitive randomized controlled trial. The 95% confidence intervals obtained in this pilot will provide the parameters required to estimate the sample size needed to detect a clinically meaningful difference in OSDI between treatment groups with adequate power.

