## Discussion

This randomized controlled trial aims to evaluate the efficacy of human umbilical cord blood (HUCB) serum eye drops in improving ocular surface health, restoring vision, and alleviating severe dry eye symptoms in patients with Sjogren’s syndrome and chemical warfare veterans. By incorporating both subjective and objective outcome measures, this study will provide a comprehensive assessment of HUCB eye drops’ therapeutic potential.

The novelty of this study lies in its investigation of HUCB eye drops as a regenerative treatment for severe dry eye, particularly in patients with underlying autoimmune and chemically induced ocular surface damage. Unlike conventional treatments, HUCB serum eye drops offer essential growth factors, neurotrophic components, and antimicrobial agents that closely mimic natural tears, potentially promoting ocular surface repair and regeneration more effectively.

One of the strengths of this study is its randomized and controlled design, which includes validated assessment tools, a well-defined patient population, and a structured follow-up protocol. The inclusion of both Sjogren’s syndrome patients and chemical warfare veterans broadens the applicability of the findings, with potential implications for other severe ocular surface disorders, such as Stevens-Johnson syndrome and industrial chemical exposure injuries.

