This study is open-label because the physical properties and storage conditions of umbilical cord blood serum differ visibly from conventional artificial tears, making participant blinding infeasible. However, the ophthalmologist and optometrist responsible for clinical assessments will remain blinded to treatment allocation to minimize measurement bias. Furthermore, objective ophthalmic parameters (TBUT, fluorescein staining, SM tube test) are included as secondary outcomes to complement the subjective OSDI score. The absence of participant blinding is acknowledged as a limitation, and results based on subjective measures will be interpreted with caution. Although a longer follow-up period would provide valuable information about the durability of treatment effects, this pilot study was designed primarily to assess short-term feasibility and preliminary efficacy. Due to resource and logistical constraints, extending follow-up beyond 60 days was not possible. The results of this trial will, however, inform the design and timing of follow-up assessments in a future larger-scale RCT with a longer observation period.

In conclusion, this study has the potential to advance treatment options for patients with severe dry eye and ocular surface damage. If successful, the findings may support the integration of HUCB serum eye drops into clinical practice as a safe and effective alternative for managing complex ocular surface diseases.

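### In Group C the serum always goes into the left eye, so treatment is aliased with side and assessor masking is not protected

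*Protocol article*

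**What the plan says.** Three places in the protocol article give the same eye assignment for Group C. The abstract describes "mustard gas veterans receiving conventional treatment in the right eye and HUCB drops in the left eye". The Intervention section gives conventional drops to the right eye and adds "one drop of cord blood serum will be dropped in the left eye, 6–10 times a day". The Randomization section states "The randomization will be performed only for groups A and B", and then: "Patients in group C will get conventional treatment in their right eyes and umbilical cord serum in their left eye". The Sample size section sets 10 patients per group. It explains that veterans serve as their own controls because few are available, but gives no reason for fixing the side.

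For the analysis of Group C, the Statistical analysis section says: "The model will include treatment (HUCB vs. conventional) as a fixed effect and a random intercept for each patient". It reads the resulting coefficient as the difference between the treatments, with a 95% confidence interval.

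On masking, the section on blinding and study termination says that "only the assessing optometrist and ophthalmologist will not be aware of the participant allocation". The Discussion repeats that "the ophthalmologist and optometrist responsible for clinical assessments will remain blinded to treatment allocation to minimize measurement bias". Neither makes an exception for Group C. The Discussion also says: "One of the strengths of this study is its randomized and controlled design".

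**The concern.** A paired-eye design controls well for differences between patients. It controls for differences between the two eyes only if the treated eye varies from patient to patient. Here it never varies, so anything that makes left eyes behave differently from right eyes during the study enters the estimated treatment effect.

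The same fixed rule weakens masking. Sealed envelopes cannot conceal a constant. Group C patients are defined by a moderate to severe mustard-gas eye injury, so an examiner may well recognise them.

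The eye-level outcomes on which the Group C contrast must rest (tear breakup time, staining score, SM tube reading, acuity) are measured or graded by an examiner. The Discussion offers assessor blinding as the safeguard against measurement bias in a trial whose participants are unblinded. At stake is the Group C effect estimate, which the pilot exists to produce for planning a later trial.

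**Working it through.** **Inputs.** Group C has 10 patients and 20 eyes (Sample size). Left eye is serum and right eye is conventional in every patient (abstract, Intervention, Randomization). The model has a treatment effect and a random patient intercept (Statistical analysis). Acuity, tear breakup time, SM tube and staining are recorded at screening, day 30 and day 60 (Table 1), and staining is scored for each eye (Secondary outcomes). The plan makes no sample size calculation, so there is no figure to reproduce. The size of any side difference is not in the documents and is assumed below.

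**1. Can treatment and side be separated?** Write the outcome as *a* (patient level) + τ (if serum) + *s* (if left eye) + error. Under the fixed rule the expected within-patient difference, left minus right, is

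(*a* + τ + *s*) − *a* = τ + *s*.

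The patient intercept cancels *a* but leaves *s*. A design matrix with columns for intercept, treatment and left eye, over 20 eyes, has rank 2 for 3 columns, and treatment and side have correlation 1.0.

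**2. What does baseline rescue?** Let the side difference be *s*₀ at screening and *s*₁ at follow-up. The between-eye difference in change from baseline has expectation

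(τ + *s*₁) − *s*₀ = τ + (*s*₁ − *s*₀).

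A stable difference (*s*₁ = *s*₀), such as unequal initial injury, drops out. A difference that arises after treatment starts does not, for example from ease of instillation or from grading coloured by expectation. The rank result in step 1 therefore describes an analysis without baseline. With baseline, the aliasing remains for *s*₁ − *s*₀.

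**3. How much could it matter?** Let *b* be the bias that remains, in units of the SD of the paired difference, and let the true treatment effect be zero. The 95% interval has half-width t(0.975, 9 df)/√10 = 2.262/3.162 = 0.715 SD. The chance that it excludes zero follows a noncentral t distribution with 9 df and noncentrality *b*√10.

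| Assumed *b* | *b*√10 | P(interval excludes 0) |
|---|---|---|
| 0 | 0 | 5% |
| 0.25 | 0.79 | 11% |
| 0.50 | 1.58 | 29% |
| 0.75 | 2.37 | 56% |
| 1.00 | 3.16 | 80% |

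The point estimate shifts by *b* in full, and a larger sample would not reduce that shift.

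**4. Masking.** An assessor who knows the rule and knows that the patient is in Group C can name the treatment of 20 of 20 eyes. With a concealed, balanced list, eye side would give a 50% guess.

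**5. Does varying the eye cure it?** With 5 patients given serum on the left and 5 on the right (252 possible allocations), the serum-minus-conventional difference has expectation τ + *s* in one half and τ − *s* in the other. Their average is τ. The treatment-side correlation falls to 0 and the rank rises to 3. In 40,000 simulated trials for each side difference (0, 0.25, 0.5 and 1.0 SD) with no treatment effect, mean bias was about 0 and the side-adjusted interval excluded zero in 4.8% to 5.2% of runs.

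**The case against.** Four points can be made for the plan.

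- **Baseline is collected.** A reader might infer that no analysis can remove a right-left difference. That goes too far: screening values exist, and a stable difference can be adjusted out. The Group C model as described does not name baseline, though an analysis plan that is not shown might add it. Even so, differences that emerge on treatment stay aliased, and no analysis plan can change that.
- **Unmasking is an inference.** A reader might conclude that the assessors know every eye's treatment. The protocol says the opposite, and the ophthalmologist who diagnoses the veterans is not said to be the assessor. The documents support only that masking can be defeated by anyone who knows the rule and recognises the patient, and that nothing described prevents this.
- **Non-randomisation is disclosed.** A reader might infer that Group C is passed off as randomised. It is not. The abstract and the Randomization section both confine randomisation to groups A and B, and the study design section treats the two populations as separate exploratory sub-studies. Only the general statement of strength in the Discussion lacks the qualifier.
- **It is an estimation pilot.** The plan disclaims any definitive reading of p-values, which lowers the stakes. It does not help with bias, because the effect estimate is itself the intended product.

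The sizes in the table are also assumed, and at 0.25 SD the distortion is modest.

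**Conclusion.** The concern stands, for Group C only. The aliasing of treatment with side is certain from the text. Its removable part (stable differences present at screening) is not removed by the model as described, and its remaining part (differences arising after treatment starts) cannot be removed by any model. The claim of assessor blinding is unprotected in this group, although the documents do not show that it has failed.

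The size is unknown. Over an assumed residual bias of 0.25 to 1.0 SD of the paired difference, with no treatment effect and 10 complete pairs, the 95% interval excludes zero in about 11% to 80% of trials instead of 5%. The only limitation on blinding that the Discussion acknowledges concerns participants. It mentions neither side nor assessor masking in Group C. The A versus B comparison is randomised between patients and is untouched.

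**What to change.** **Group C patients not yet treated.** Randomise which eye receives serum, balanced left and right, from a list held by the external allocator and kept from the assessing optometrist and ophthalmologist. Include side and each eye's baseline value in the mixed model.

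**Group C patients already treated under the fixed rule.** Recruitment began on April 1, 2025 and was planned to end on July 31, 2025, so this may be most or all of them. Adjust for each eye's baseline. Report Group C as a non-randomised, side-confounded comparison without protected assessor masking.

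**Text.** Qualify the blinding statements in the section on blinding and study termination and in the Discussion so that they do not claim protected assessor masking for Group C eyes treated under the fixed rule. Limit the randomised-design strength statement to groups A and B.

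**Cost.** One more short list, eye-specific labelling and a protocol amendment. There is a slightly higher risk of instilling into the wrong eye, which labelling should limit. Baseline adjustment and the changes of wording need no new data.
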